#### Baseline computer-tailored session

The baseline computer-tailored session consisted of a shortened version of a previously tested CT program that was found to be more effective in increasing smoking cessation than the provision of generic advice and information [8,25]. The baseline session was intended to increase the respondents' motivation to quit smoking and to encourage the respondents to set a quit date in the next few months. Respondents received tailored feedback on the perceived advantages and disadvantages of quitting. Tailored feedback was offered with regard to the different pros of quitting (e.g. decreased likelihood of diseases) in order to convince the respondents of the advantages of quitting. Tailored feedback further addressed the disadvantages of quitting (e.g. withdrawal symptoms) in order to combat possible negative existing beliefs. With respect to the respondent's perceived social support, tailored feedback dealt with how to deal with smokers in their environment (e.g. asking them not to smoke in their environment in order to avoid a relapse). Furthermore, respondents received feedback on their perceived self-efficacy, the importance of self-efficacy for successful quitting and tips for increasing self-efficacy. Lastly, information was provided on how to plan quitting (e.g. planning a quit date and using smoking cessation aids). Depending on the readiness to quit within one month or not, respondents received feedback in one of the two routings that are explained in detail below.

#### Routing 1

Respondents who were ready to quit in the next month were directed into routing 1. After the baseline questionnaire, respondents in session 1 were asked to set a quit date. Respondents were requested to choose a quit date between eight days and one month from baseline. At the end of the first session, smokers were informed by e-mail that they would be invited for the next session of the program one week before their quit date in order to receive new support and help in preparing their quit attempt in the following days.

One week before their quit date respondents were invited by e-mail to follow the next session of the program. The second session was aimed at preparing the smoker to quit successfully and to be prepared for the difficulties that might arise after quitting. Respondents were first asked to fill out a short questionnaire on self-efficacy and action planning items. Several studies identified a low level of self-efficacy as a good predictor of smoking relapse (Elfeddali I, Bolman C, Candel MJJM, Wiers RW, De Vries H: Preventing smoking relapse via Internet-based computer tailored feedback: 12 month results of the SQ4U-study, submitted) [40-42]. Therefore, respondents received feedback on how to increase self-efficacy. Tailored feedback on self-efficacy was provided in order to help the respondent to gain confidence to quit and to help him/her to deal with the possible difficulties and negative consequences of their quit attempt. Next, respondents were encouraged to make preparatory plans for their quit attempt. Tailored feedback addressed the advantages of making plans in advance and respondents were furthermore stimulated to think about concrete plans (e.g. removing ashtrays, asking guests not to smoke and thinking about difficult situations they might encounter after quitting). Lack of preparatory planning has been shown to be a good predictor of smoking relapse and preparing for quitting has been shown to increase smoking cessation [8]. The second session not only aimed at preparing the smoker to quit successfully (by encouraging preparatory planning) but also to prepare the smoker to cope with the challenges/difficulties that might arise after quitting. This so-called coping planning has been shown to be a helpful strategy for dealing with high-risk situations [43]. To encourage coping planning respondents were first asked to choose from a list of eleven risk situations (e.g. I find it difficult not to smoke if I am angry, I find it difficult not to smoke when I see another person enjoying a cigarette) the three most personally relevant high-risk situations. Next, respondents were asked to indicate whether they had already thought about how to deal with these high-risk situations. If they had not thought about coping plans, respondents were instructed to formulate specific coping plans for their personal high-risk situations. Examples were given of how to make concrete plans (e.g. Next time you feel angry, instead of smoking a cigarette, go outside and have a walk).

Session 3 took place three days after the quit date of the respondent. At that time, respondents were invited by e-mail to turn to the CT program again and to fill out a brief questionnaire on self-efficacy and coping planning items. The third session was aimed at encouraging the respondent again to think about possible coping plans in order to deal with high-risk smoking-related situations. The same strategy was used as in session 2. Respondents were also asked about their smoking behaviour since their quit date. In cases of lapse/relapse the respondent was told that smoking cessation is a process in which lapses may occur and that they can be used positively in continuing the quit attempt. Respondents were also encouraged and invited to continue their quit attempt or to plan a new quit date. This strategy derived from a CT relapse prevention preprogram that has shown to be effective in preventing relapse (Elfeddali I, Bolman C, Candel MJJM, Wiers RW, De Vries H: Preventing smoking relapse via Internet-based computer tailored feedback: 12 month results of the SQ4U-study, submitted).

Two weeks after the quit date respondents were invited for session 4. Respondents were instructed to fill out again a brief questionnaire on self-efficacy and coping planning items. The same procedure was used as in session 2 and 3 of the program. Furthermore, pros and cons of quitting were assessed again as in session 1. This was done in order to encourage the respondents to rethink about the pros and cons of smoking and quitting that they perceived and to assess whether respondents had acquired possible new pros of quitting since the first session of the program.

In sessions 5 and 6, after four and eight weeks, a similar strategy was used to that in session 4. During the last three sessions, respondents could still choose to receive tailored feedback on different items (such as how to cope with negative moods or how to cope with high-risk situations). This option was provided since we expected them to encounter different problems throughout their quit attempt. In all these sessions smokers who had reverted to smoking were invited and encouraged to restart their quit attempt.

#### Routing 2

Respondents who were not ready to quit in the next month followed routing 2. At the end of session 1, that followed immediately after the baseline session, respondents were encouraged to use the next month to reflect on their quitting intention and the tailored information they received during session 1. After one month these smokers received an e-mail with an invitation for the second session. In session 2 the respondent was asked about his/her smoking behaviour. Subsequently respondents again received feedback on the perceived advantages and disadvantages of smoking and quitting and how best to obtain social support from their environment. At the end of the session smokers were asked to indicate their readiness to quit in the next month. Respondents who were ready to quit in the next month and ready to plan a quit date were sent to routing 1. Respondents not intending to quit in the next month were informed that they would receive an invitation for session 3 one month later to reassess their smoking behaviour and their motivation to quit.

As in session 2, respondents received in session 3 tailored feedback on the perceived advantages and disadvantages of smoking and quitting and how best to obtain social support from others. Smokers were again encouraged to quit and were asked at the end of the session to indicate their intention to quit in the next month. Respondents ready to quit within the next month and ready to plan a quit date were sent to routing 1. Smokers not prepared to plan a quit date within a month received an empathic message, indicating that it was respected that they were not ready to quit smoking and that we would therefore send no further e-mails at this stage.

Finally, at the end of the program, all respondents were informed that they would receive an invitation (by e-mail) after six and twelve months to fill out a brief follow-up questionnaire about their smoking behaviour and a process evaluation questionnaire on the programs after 6 months.

### Control group

The control group received brief generic text advice about smoking cessation. The content of the generic text was similar to the experimental conditions. Although brief advice was given on how to quit successfully, the generic text advice was not tailored to personal factors and respondents in the intervention group all received the same information. Furthermore, respondents were not provided by e-mail with an overview of the brief non-tailored text advice.

### Outcomes and biochemical validation

#### Primary outcome measurement

Primary outcome measures of this study measured at six and twelve months after baseline were seven-day point prevalence abstinence from smoking (PPA), continued abstinence and prolonged abstinence. Seven-day point prevalence was defined as not having smoked during the last seven days (measured from follow-up). Continued abstinence was defined as not having smoked since the last quit date, whereas prolonged abstinence took into account a grace period of two weeks [28,44]. During this grace period re-initiating of smoking behaviour after the quit date was not defined as a relapse. All outcome variables were measured according to the definitions in Hughes et al. [28,44]. Smoking during the last seven days and after the personal quit date was coded as relapse (0), whereas non-smoking during the last seven days and since the quit date was coded as abstinence (1).

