### Statistical analysis

#### Sample size calculation

Sample size calculations were based on the ability to detect 10% differences between the three conditions with a power of 0.80 and an alpha of 5%. To calculate the sample size, seven-day point prevalence abstinence at the six- and twelve-month follow-up was taken as the base since it is considered to be the most sensitive and valid measure of smoking cessation [45].

Power calculations were made separately for LSES and HSES groups. For the LSES group we expected that the video condition will result in an 18% quit rate, and the text condition in an 8% quit rate, requiring 176 participants in both conditions. For the HSES group we expected quit rates of 22% in the text-based condition and 12% in the video-based condition, requiring 220 smokers for both conditions.

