#### Analysis

We will conduct logistic regression analysis at six and twelve months to assess program effects on the main outcome variables. We will further perform linear regression analysis and covariance analysis to assess effects on secondary outcome variables at six and twelve months. We will correct for baseline factors (e.g. demographics, smoking behaviour, attitude, intention) in both types of regression analyses by adding these variables as possible confounders. Interaction effects of experimental condition (text vs. video) and SES will be explored by moderation in the logistic regression analysis since we expect an interaction effect between SES and condition.

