## Discussion

The paper describes two multiple computer-tailored smoking cessation programs and the design of an efficacy study that will be conducted to test the effects of the programs on smoking cessation. The computer-tailored e-health approaches are currently tested by Dutch smokers who are motivated to stop smoking. The tailored messages are the same in both conditions; the two conditions only differ in the mode of delivery. One experimental condition uses video-driven messages whereas the other condition uses text-driven messages. The two experimental conditions (video vs. text) will be compared with each other and with a control condition which receives general smoking cessation advice. Furthermore, the effects of the two different multiple tailored smoking cessation programs will be tested among smokers with a lower and higher socio-economic background.

The present study has several strengths. First, it addresses the efficacy of two computer-tailored programs by means of a strong experimental design. A randomized control trial was used to exclude possible biases with regard to assignment of respondents to the different conditions. Allocation of the different conditions was performed automatically with the Tailor Builder computer software.

Second, the intervention is one of the first programs to test video-based messages as a potential new communication strategy for LSES smokers. So far computer-tailored smoking cessation interventions have tended to rely on text-based messages. Several studies however suggest that videos may be more effective in attracting attention and stimulating comprehension, especially in LSES smokers [22].

Third, an important strength of our smoking cessation programs concerns the inclusion of multiple tailored feedback moments. Tailored information has been shown to be more likely to be read, remembered and considered personally relevant. Our study made use of a multiple computer-tailored smoking cessation intervention with different feedback moments. Although previous programs did focus on smoking cessation tailored messages, few of them provided smokers with multiple tailored feedback moments.

Finally, one strategy the study used to collect participants was via the GP setting. The GP is considered as an important access point to many smokers [46]. Advice from GPs is an effective way to help smokers to quit and is seen as valuable by the Dutch patient [47].

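### Three unranked primary outcomes at two time points and three pairwise comparisons give up to 18 primary tests, but the sample size allows for none of this multiplicity

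*Protocol article*

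**What the plan says.** All references are to the protocol article.

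- **Primary outcome measurement:** the primary outcomes "measured at six and twelve months after baseline were seven-day point prevalence abstinence from smoking (PPA), continued abstinence and prolonged abstinence". No order is given, and nothing says whether success needs one of them or all of them.
- **Analysis:** "We will conduct logistic regression analysis at six and twelve months to assess program effects on the main outcome variables". Both time points are therefore analysed. No significance level per test is stated.
- **Discussion:** "The two experimental conditions (video vs. text) will be compared with each other and with a control condition which receives general smoking cessation advice". That is three pairwise comparisons.
- **Sample size calculation:** a single alpha, 5%, is given, introduced by the words "Sample size calculations were based on the ability to detect 10% differences between the three conditions with a power of 0.80 and an alpha of". For the outcome, "seven-day point prevalence abstinence at the six- and twelve-month follow-up was taken as the base". Also, "Power calculations were made separately for LSES and HSES groups". In the lower-SES group, "the video condition will result in an 18% quit rate, and the text condition in an 8% quit rate, requiring 176 participants in both conditions"; in the higher-SES group, "quit rates of 22% in the text-based condition and 12% in the video-based condition, requiring 220 smokers for both conditions".

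**The concern.** The choice of primary outcome decides which result can be called the trial's answer. Here six outcome-by-time pairs have equal standing, each open to three comparisons. The only error rate in the article is one alpha of 5%, attached to the sample size. As the text stands, a significant result on any of the primary tests could be reported as a positive primary finding, and the chance that this happens by luck alone is well above 5%.

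Sizing on seven-day abstinence does not settle the matter. That calculation names both follow-ups and is done separately in two SES groups, so it does not single out one primary test.

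**Working it through.** **1. Number of primary tests.** 3 outcomes × 2 times × 3 pairwise comparisons = 18, before any SES split and without the condition-by-SES interaction.

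**2. Reproducing the stated sample sizes.** Two proportions, 1:1, pooled variance, two-sided 5%, power 0.80, no continuity correction:

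n per arm = [z(0.975)·√(2p̄(1−p̄)) + z(0.80)·√(p1(1−p1) + p2(1−p2))]² / (p1−p2)²

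- Lower SES, 18% vs 8%, p̄ = 0.13: (1.960·√0.2262 + 0.8416·√0.2212)² / 0.01 = 176.4 (stated 176).
- Higher SES, 22% vs 12%, p̄ = 0.17: (1.960·√0.2822 + 0.8416·√0.2772)² / 0.01 = 220.3 (stated 220).

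The unpooled version (174 and 218) and the arcsine version (172 and 218) are also within 3%. One-sided tests (139 and 174) and continuity-corrected tests (196 and 240) do not reproduce the figures. Read as totals over two arms, the stated numbers would give power of only about 0.51. They are therefore per-arm figures for one unadjusted two-sided 5% comparison in each SES group.

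**3. Chance of at least one false positive with each test at two-sided 5%.** Simulation under no effect: three equal arms; six correlated normal outcome-by-time statistics per arm, with correlation between outcomes times correlation between times; three pairwise differences divided by √2; rejection if |z| > 1.96; 200,000 replicates. The correlations are assumptions, since the article gives none.

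| Correlation: outcomes / times | All 18 tests | Seven-day abstinence, 2 times × 3 contrasts | Seven-day abstinence, video vs text, 2 times |
|---|---|---|---|
| 0 / 0 | 54.3% | 23.1% | 9.8% |
| 0.5 / 0.5 | 45.9% | 21.2% | 8.9% |
| 0.7 / 0.6 | 39.5% | 20.6% | 8.7% |
| 0.8 / 0.6 | 36.0% | – | – |
| 0.8 / 0.7 | 34.5% | 19.6% | 8.3% |
| 0.9 / 0.7 | 30.3% | – | – |
| 0.9 / 0.8 | 28.3% | 18.3% | 7.8% |
| 0.95 / 0.9 | 23.3% | 16.7% | 7.0% |

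(A dash means that the narrower set was not tabulated in that run.) One outcome at one time with three contrasts gives about 12%, whatever the correlations. Testing in two SES groups would raise all these figures.

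**4. If alpha were split instead.** The same formula with a Bonferroni alpha:

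| Tests covered | Alpha per test | n per arm, lower / higher SES | Power at 176 / 220 per arm |
|---|---|---|---|
| 3 | 0.0167 | 236 / 295 | about 66% |
| 6 | 0.0083 | 273 / 341 | about 56% |
| 18 | 0.0028 | 331 / 413 | about 42% |

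**The case against.** - **The test-level 5% is not stated.** The only alpha is in the sample size paragraph, and a multiplicity rule is commonly left to an analysis plan, which is not shown here. This stands: the absence of an adjustment is not itself the finding. The ranking of primary outcomes, however, is a choice that the protocol has made, and it left six outcome-by-time pairs level. An unseen plan that split alpha would also leave the stated sample sizes short of 80% power.
- **Pairwise testing is not spelled out in the Analysis section.** The three comparisons come from the Discussion. With three arms, an overall two-degree-of-freedom test before the pairwise contrasts would hold error at about 5% for one outcome at one time, in place of 12%. The article does not describe that step, and it would not deal with the six outcome-by-time pairs.
- **A reader might infer a 60% error rate**, from 1 − 0.95^18 = 0.603. The documents do not support it. The three contrasts share arms, so the tests cannot be independent, and the figure is 54% even with uncorrelated outcomes and times. Continued and prolonged abstinence differ only by a two-week grace period, so high correlation is the more plausible case.
- **A reader might infer that the error of the trial's main claim has been measured.** The stated aim is the difference between video and text by SES. The count of 18 covers neither the interaction nor the SES groups. For seven-day abstinence, video against text, the excess is modest: 7% to 10%.
- **An all-must-succeed rule** would remove the need to correct across outcomes and times. No such rule is stated.

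**Conclusion.** The concern holds in a bounded form. The protocol fixes its primary outcomes badly: three outcomes at two times, unranked, with three conditions compared pairwise, against a sample size that covers one unadjusted two-sided 5% comparison per SES group.

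If each test is made at 5%, the chance of at least one false-positive primary result is about 23% to 36% for assumed correlations of 0.8 to 0.95 between outcomes and 0.6 to 0.9 between times. Narrower sets of tests give 17% to 23% (seven-day abstinence, three contrasts, two times), 12% (one outcome, one time, three contrasts) and 7% to 10% (seven-day abstinence, video against text, two times). Every one exceeds 5%, so the conclusion depends neither on the count of 18 nor on the exact correlations. It does depend on the 5% per test inferred from the sizing.

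**What to change.** Name seven-day point prevalence abstinence at twelve months as the single primary outcome. The article already supports this choice: it is the outcome used for sizing and in the economic evaluation, and twelve months is the only time point with cotinine validation. Make six-month seven-day abstinence, and continued and prolonged abstinence at both times, secondary.

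State in advance how error is controlled over the few remaining primary contrasts. The order or procedure is the sponsor's choice, but it should not place the comparisons with control behind the condition-by-SES interaction. The Analysis section only plans to explore that interaction, while efficacy against control is a stated objective. If the interaction came first and failed, neither program could be formally tested against control.

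If alpha is split instead of ordered, restate the power. Bonferroni over three contrasts needs about 236 and 295 per arm rather than 176 and 220.

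Naming the outcome costs wording only, with no extra participants. The real downside is that a significant six-month, continued-abstinence or prolonged-abstinence result alone could no longer be called a positive primary result.

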#### Secondary outcome measures

Secondary outcome variables measured at six and twelve months after baseline included 24-hour point prevalence abstinence (having smoked during the last 24 hours; 1 = no; 0 = yes), having made a serious quit attempt (not having smoked for at least 24 hours; 1 = no; 0 = yes) and changes in smoking behaviour since baseline measurements [44]. All respondents were further asked to fill out a process evaluation questionnaire at the six-month follow-up to evaluate their experience of the program.

#### Biochemical validation

At the last follow-up measurement (12 months after baseline) self-reports regarding cessation will be biochemically validated by means of a cotinine test. We aim to validate self-reports randomly in a subsample of participants who have indicated abstention from smoking. At least 50% of this sample will be invited to participate. We aim to conduct the biochemical validation within one week after 12-month follow-up measurement. Respondents reporting abstention at the 12-month follow-up will be approached by a research assistant to make an appointment for the cotinine test (e.g. at home or at work). Saliva of the respondents will be collected with a swab stick and will be applied to a test strip. Respondents who decline to undergo the test will be asked by the research assistant for the reason(s) why.

